#### Blinding assessment

2.9.4

Immediately after the final treatment session (within 5 minutes prior to post-treatment outcome assessments), all participants complete a masking evaluation. Participants are asked a single binary question: “Do you believe you received the authentic acupuncture intervention?” with three response options: “Yes”, “No”, or “Uncertain”.

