#### Manual acupuncture group

2.7.1

The Manual Acupuncture (MA) group will receive treatment using sterile, single-use stainless steel needles (Hwato brand; 0.25 mm diameter needles in 25 mm or 40 mm lengths, and 0.30 mm diameter needles in 75 mm length). The details of acupoint locations and needling techniques are presented in **Table 2**. Treatment alternates between two fixed acupoint sets, commencing with Set A. Set A (supine position) comprises CV12 (Zhongwan), KI16 (Huangshu), CV4 (Guanyuan), KI12 (Dahe), EX-CA1 (Zigong), ST36 (Zusanli), and SP6 (Sanyinjiao). Set B (prone position) includes BL23 (Shenshu), BL33 (Zhongliao), and KI3 (Taixi). Based on the participant’s baseline TCM pattern diagnosis, which is categorized into four distinct patterns, two adjunct points will be added per session according to the following predefined protocol: (1) Kidney Deficiency Pattern: KI6 (Zhaohai) and LR3 (Taichong) (supine); GV4 (Mingmen) and BL18 (Ganshu) (prone); (2) Phlegm-Dampness Pattern: ST40 (Fenglong) and SP9 (Yinlingquan) (supine); BL20 (Pishu) and BL21 (Weishu) (prone); (3) Blood Stasis Pattern: LI4 (Hegu) and SP10 (Xuehai) (supine); BL15 (Xinshu) and BL17 (Geshu) (prone); (4) Liver Qi Stagnation Pattern: LR5 (Ligou) and LR3 (Taichong) (supine); BL18 (Ganshu) and BL19 (Danshu) (prone).

With the patient in an appropriate position, the local skin will be routinely disinfected. BL33 (Zhongliao) is inserted obliquely inferioromedially to a depth of 2.0-2.5 cun to target the third posterior sacral foramen. All other acupoints will be perpendicularly inserted to a standard depth of 1.0-1.2 cun. All needles will be manually manipulated to elicit the characteristic de qi sensation (a composite sensation of soreness, numbness, distension, or heaviness at the acupoint). All acupoint areas are disinfected with 75% alcohol swabs before needling. Needles will be retained for 20 minutes.

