#### Sham acupuncture group

2.7.2

The Sham Acupuncture (SA) group will receive treatment at predefined non-acupoint (NA) locations using sterile, single-use stainless steel needles (Hwato brand; 0.25 mm diameter, 25 mm length). The locations of these sham points, which are near but distinct from conventional acupoints, are specified in **Table 3** (e.g., 1 cun lateral to CV4).

**Table 3 T3:** Intervention protocol for SA group.

Component	Acupoint / sham point name	Location	Needling details
Set A (Supine)	NA-1	1.0 cun lateral to the left of CV12.	Needle: Φ0.25×25 mm sterile needle. Depth: Superficial insertion of 2–3 mm.
	NA-2	1.0 cun lateral to KI16.	Same as above.
	NA-3	1.0 cun lateral to the right of CV4.	Same as above.
	NA-4	1.0 cun lateral to KI12.	Same as above.
	NA-5	10 mm lateral to ST36.	Same as above.
	NA-6	Midpoint between SP6 and the medial border of Achilles tendon.	Same as above.
Set B (Prone)	NA-7	Midpoint between BL23 and the inner line of Bladder Meridian (approx. 0.75 cun lateral).	Same as above.
	NA-8	1.0 cun lateral to BL33.	Same as above.
	NA-9	Anterior border of Achilles tendon, level with KI3.	Same as above.

Treatment will alternate between two standardized sets of sham points per session, starting with Set A (supine position), which comprises non-acupoints near CV12 (NA-1), KI16 (NA-2), CV4 (NA-3), KI12 and EX-CA1 (NA-4), ST36 (NA-5), and SP6 (NA-6). Set B (prone position) includes non-acupoints near BL23 (NA-7), BL33 (NA-8), and KI3 (NA-9). No pattern-based adjunct points will be applied.

With the patient in a suitable position, the skin at each sham point will be routinely disinfected. All sham points receive identical alcohol disinfection before needling. A needle will be inserted superficially to a depth of 2–3 mm. No needle manipulation will be performed, and no de qi sensation will be sought or elicited. The needle will be retained for 20 minutes.

Non-acupoint shallow needling was selected as the sham control to provide a credible blinding experience without specialized devices, while minimizing specific therapeutic effects by avoiding de qi and deep insertion. To minimize unblinding risk, the insertion depth (2–3 mm) and needle type were standardized across all sham sessions. All participants are informed that “acupuncture sensations may vary from person to person” to reduce expectation bias.

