### Outcome measurement

2.9

All outcome measurements will be scheduled according to the study timeline (**Table 1**). Baseline assessments will be performed before randomization and prior to the first treatment. Primary and secondary outcomes are assessed at the end of the 12-week treatment period (Week 12) and at the end of the 12-week follow-up period (Week 24).

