#### Primary outcome

2.9.1

The primary outcome is the cycle ovulation rate (COR). To account for the inherent irregularity of menstrual cycles in PCOS, the 12-week treatment period is divided into three standardized 28-day (4-week) time windows (i.e., Weeks 1-4, 5-8, and 9-12), each serving as an observation unit for detecting ovulation. COR is calculated using the following formula: COR (%) = (Number of 28-day time windows with ultrasound-confirmed ovulation/Number of completed full 28-day time windows) × 100% (19, 20). For participants who complete the full 12-week treatment period, the denominator is 3. For participants who withdraw early, the denominator is the number of full 28-day time windows completed before withdrawal. Participants who complete at least one full 28-day time window will be included in the primary analysis. Ovulation is confirmed by transvaginal ultrasound (TVUS), which serves as the gold standard. A window is considered ovulatory when TVUS documents the development of a dominant follicle (≥18 mm in diameter) followed by its subsequent collapse or disappearance, accompanied by the appearance of free fluid in the pouch of Douglas (29). Given that women with PCOS often have prolonged and irregular menstrual cycles, urinary LH test strips will be used daily to optimize the timing of ovulation monitoring. For each menstrual cycle, testing will begin on day 10–12 of that cycle and continue until ovulation is confirmed or the cycle ends. Once a positive LH test is observed, transvaginal ultrasound will be performed to confirm follicular rupture and ovulation. For participants who do not achieve a positive LH test, daily LH test strip use will continue until the end of that menstrual cycle. Daily basal body temperature (BBT) charting will be maintained as a supplementary record.

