#### Secondary outcomes

2.9.2

Menstrual cycle characteristics will be evaluated using two measures: 1) mean menstrual cycle length, calculated as the total number of days in the observation period (84 days for the 12-week treatment period, and 84 days for the 12-week follow-up period) divided by the number of menstrual cycles that occurred during that period. A menstrual cycle is defined as the interval from the first day of one menstrual bleeding to the day before the next menstrual bleeding. If no menstrual bleeding occurs during the entire observation period, the mean cycle length is considered missing, and the participant will be classified as having amenorrhea for that period. This value will be derived from participant-maintained calendars, and the average during treatment and follow-up will be compared to the self-reported baseline.; and 2) the menstrual cycle recovery rate, defined as the proportion of participants achieving a normalized cycle length of 21–35 days.

The sex hormone profile, measured in the early follicular phase (days 2–5 of a spontaneous cycle), includes the Free Androgen Index (FAI) (calculated as [total testosterone/sex hormone-binding globulin (SHBG)] × 100) (30) and the LH/FSH ratio.

The metabolic profile comprises three domains: 1) Anthropometric measures: body weight, height (for BMI), waist circumference (WC), and hip circumference (HC) to calculate the waist-to-hip ratio (WHR); 2) Glucose metabolism: fasting plasma glucose (FPG) and fasting insulin (FINS), with insulin resistance estimated by the Homeostatic Model Assessment index (HOMA-IR), a marker of insulin resistance, is calculated as (FINS × FPG)/22.5 (31); 3) Lipid profile: Total cholesterol (TC), triglycerides (TG), high-density lipoprotein cholesterol (HDL-C), and low-density lipoprotein cholesterol (LDL-C).

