#### Safety outcomes

2.9.5

All adverse events (AEs) will be actively screened and documented at every visit through physician inquiry and patient self-report. This includes common acupuncture-specific AEs (e.g., local bleeding, hematoma, pain, bruising, fainting, or prolonged post-needling sensation) and general AEs (e.g., dizziness, nausea). The causality, severity, duration, management, and outcome of each AE will be documented in the Case Report Form. A Serious Adverse Event (SAE) is defined as any event that is fatal, life-threatening, requires hospitalization, or results in significant disability, and must be reported to the principal investigator and ethics committee within 24 hours of awareness. The frequency and severity of all AEs will be compared between MA and SA arms at trial completion.

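### Read literally, the Week 12 self-report scales are completed minutes after a last session that differs by arm, so any acute effect of that session is mixed with the effect of the 12-week course

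*Protocol article*

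**What the plan says.** Section 2.9.4 fixes an order at the end of treatment: "Immediately after the final treatment session (within 5 minutes prior to post-treatment outcome assessments), all participants complete a masking evaluation". The order is therefore last session, masking question, then post-treatment assessments within 5 minutes.

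The general timing in section 2.9 is looser: "Primary and secondary outcomes are assessed at the end of the 12-week treatment period (Week 12) and at the end of the 12-week follow-up period". It gives no day or interval relative to a session. For the start of the trial the same section says: "Baseline assessments will be performed before randomization and prior to the first treatment".

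The Post-treatment (Week 12) column of Table 1 contains the blinding assessment together with PCOSQ, SAS, SDS, PGIC, anthropometrics, metabolic parameters and reproductive hormones.

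The session itself differs by arm. In the manual acupuncture group (section 2.7.1), "All needles will be manually manipulated to elicit the characteristic de qi sensation". In the sham group (section 2.7.2), "A needle will be inserted superficially to a depth of 2–3 mm", with no manipulation and no de qi sought.

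**The concern.** The Week 12 comparison of SAS, SDS and PCOSQ is meant to show what 12 weeks of treatment did. If the scales are filled in minutes after needling, they may also pick up how the participant feels after that one session, and that session is not the same in the two arms.

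The effect could go either way: relaxation after a session could add to an apparent benefit, and soreness or light-headedness could hide one. The protocol does not claim either, but section 2.9.5 has staff screen for "local bleeding, hematoma, pain, bruising, fainting, or prolonged post-needling sensation" as well as dizziness and nausea, and the limitations paragraph of the Discussion accepts that sensations may differ between groups.

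The statistical model does not help. Section 2.13 adjusts continuous secondary outcomes for baseline and center. An effect that arises after randomization and differs by arm is part of the treatment contrast, so baseline adjustment leaves it in place. At Week 24 the last session lies 12 weeks back, so a transient Week 12 shift would disappear and could be read as loss of benefit.

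The order also puts the masking question directly before the self-ratings. That is a separate matter: moving the question alone would still leave the ratings minutes after needling.

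**Working it through.** **Which Week 12 outcomes are exposed.** Setting section 2.9.4 beside the definitions in sections 2.9.1 to 2.9.3:

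| Outcome | Timing in the protocol | Exposed? |
|---|---|---|
| Cycle ovulation rate (primary) | "the 12-week treatment period is divided into three standardized 28-day (4-week) time windows" | No, accumulates over 12 weeks |
| Cycle length, recovery rate | Calendar over 84 days | No |
| FAI, LH/FSH | "measured in the early follicular phase (days 2–5 of a spontaneous cycle" of menstruation | No, tied to cycle day; will seldom be the day of the last session |
| Fasting glucose, insulin, lipids | Glucose and insulin stated as fasting; no day given relative to the last session | Cannot be told |
| BMI, waist, hip | Week 12 | No acute route is evident |
| SAS, SDS, PCOSQ | Week 12, post-treatment column | Yes, on the literal reading |
| PGIC | Week 12; asks about change since trial start | Yes, but less sensitive |

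The hormone row also shows that section 2.9.4 cannot govern every Week 12 assessment, so its wording and that of sections 2.9 and 2.9.2 need reconciling.

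**Sample size used.** The plan's own figure (section 2.12) is for the primary outcome: 65% versus 40%, two-sided 0.05, power 80%. The pooled-variance chi-square formula without continuity correction gives 62 per group, and 62/0.80 = 77.5, rounded up to 78. Both figures reproduce. They serve here only as the range of women per arm contributing Week 12 scales.

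**Assumed acute shift.** The documents give no size, so a range is taken. Assume no lasting effect and an acute between-arm shift of δ SD. For a baseline-adjusted comparison with baseline correlation r (also assumed):

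- SE = √(2(1 − r²)/n), in SD units
- P(p<0.05) = Φ(δ/SE − 1.96) + Φ(−δ/SE − 1.96)

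With r = 0.5:

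- n = 62: SE = √(1.5/62) = 0.156
- n = 78: SE = √(1.5/78) = 0.139

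| δ (SD) | n = 62 | n = 78 |
|---|---|---|
| 0.1 | 9.9% | 11.1% |
| 0.2 | 25.1% | 30.3% |
| 0.3 | 48.8% | 58.1% |

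For r from 0.3 to 0.7, and n from 62 to 78, the ranges are 9–14%, 22–42% and 42–75%. Without any covariate gain (r = 0), which is the relevant case for PGIC because it has no baseline, they are 9–10%, 20–24% and 39–47%. The nominal rate is 5% throughout.

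**The case against.** **The article is condensed, and section 2.9.4 is about the masking question.** The order of procedures within a visit is commonly left to a site manual, and section 2.9 with Table 1 is the outcome schedule. This would be decisive if the article were silent. It is not: it states a sequence and a 5-minute interval, and nothing exempts the questionnaires.

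**Most outcomes are not momentary.** This largely stands. A reader might infer that all Week 12 outcomes are taken minutes after needling. The documents do not support that for the primary outcome, the cycle measures or the hormones. A reader might also infer that glucose and insulin are affected; section 2.9.4 names no blood sample and section 2.9.2 gives no sampling day. Several PCOSQ domains, such as hirsutism and acne, are also unlikely to move within minutes, so SAS, SDS and the emotional content of PCOSQ are the most exposed.

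**No acute effect is shown.** This stands too. The autonomic mechanism in the Introduction is a hypothesis about ovulation, and the list in section 2.9.5 gives examples of events to look for, without frequencies. The calculation shows what a shift would do if it existed, not that it exists.

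**The last session belongs to the course.** It does, and including its immediate effect could be a deliberate choice of what to estimate. The protocol does not present it as one. Week 24 is free of same-day needling, but it measures persistence and cannot replace a clean end-of-treatment value.

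**Conclusion.** The point holds for the Week 12 self-report scales: SAS, SDS, PCOSQ and, less sensitively, PGIC. On the literal wording they follow within minutes of an arm-specific session, while baseline and Week 24 do not. Any acute effect would be mixed with the effect of the course and could pass for fading by Week 24.

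The stronger reading, that a Week 12 difference would reflect one session in place of 12 weeks of treatment, is not supported, because the size of any acute effect is unknown. The 10% to 58% range rests on assumed shifts of 0.1 to 0.3 SD, no lasting effect, a baseline correlation of 0.5 and 62 to 78 women per arm.

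The primary analysis and the sample size are untouched. The point concerns secondary outcomes only, but it should be settled before Week 12 data are collected, because the analysis cannot separate the two effects afterwards.

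**What to change.** 1. State in sections 2.9 and 2.9.4 that, in both arms, the Week 12 questionnaires are completed before the needling of the last session, and that the same holds for any other assessment or blood sample that falls on that day.
2. State that the masking question is asked after all participant-reported outcomes. With the questionnaires done first, it can stay directly after the last session.
3. Reconcile the timing wording of sections 2.9, 2.9.2 and 2.9.4: keep hormones tied to the cycle day, and give the sampling day for fasting glucose and insulin relative to the last session.

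The cost is a few lines in the protocol and visit instructions; no extra visit or staff is needed. The downside is that these Week 12 values follow 35 sessions instead of 36, so the description of Week 12 in section 2.9 as the end of the treatment period needs matching wording.

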#### Safety outcomes

2.9.5

All adverse events (AEs) will be actively screened and documented at every visit through physician inquiry and patient self-report. This includes common acupuncture-specific AEs (e.g., local bleeding, hematoma, pain, bruising, fainting, or prolonged post-needling sensation) and general AEs (e.g., dizziness, nausea). The causality, severity, duration, management, and outcome of each AE will be documented in the Case Report Form. A Serious Adverse Event (SAE) is defined as any event that is fatal, life-threatening, requires hospitalization, or results in significant disability, and must be reported to the principal investigator and ethics committee within 24 hours of awareness. The frequency and severity of all AEs will be compared between MA and SA arms at trial completion.

### Data management

2.10

All the trail data will be initially recorded on paper-based Case Report Forms (CRFs) at each site and subsequently entered into a secure, web-based Electronic Data Capture (EDC) system by trained coordinators following a specific data entry guide. The data quality is ensured through programmed range/logic checks within the EDC system, manual medical review by a clinical research associate (CRA) — including 100% source data verification for the primary outcomes — and regular audits by a dedicated data manager. All modifications to the database are logged with a timestamp, user identification, and a reason for change. Prior to the database lock, a comprehensive data management report will be prepared, reviewed, and approved by investigators and statisticians in a data review meeting to resolve queries and finalize the analysis dataset. The locked database, in SAS format along with its structure documentation and codebooks, will be delivered to the statistician for analysis. All study documents will be kept confidential by the lead research unit. Investigators and the ethics committee may access individual medical records as permitted by law, but any public reports will strictly protect participant anonymity, with every effort made to safeguard personal health information within legal bounds.

### Quality control

2.11

To ensure protocol adherence and data integrity across all six centers, a multi-layered quality control system will be implemented. This system encompasses centralized, mandatory training and certification for all study personnel prior to the site initiation, pre-initiation site visits to confirm operational readiness, and routine, independent on-site monitoring to verify source data, informed consent, and protocol compliance. Furthermore, random fidelity checks of audio/video-recorded acupuncture sessions will be conducted by an independent expert to assess treatment adherence. The overall trial conduct, safety data, and protocol amendments will be overseen by an independent steering committee comprising clinical, methodological, and acupuncture experts.

### Sample size

2.12

The sample size calculation was based on the primary outcome, the cycle ovulation rate (COR). Based on a systematic review of prior studies (15, 19, 20) and our pilot data[Trial Registration Number: ChiCTR2300073494], we anticipated a COR of 65% in the MA group and 40% in the SA group at the end of the treatment. Using a two-sided Chi-square test with a significance level (α) of 0.05 and a power (1-β) of 80%, the required sample size per group was calculated to be 62 participants. Accounting for an estimated 20% dropout rate over the 24-week study period, the final target sample size was 78 participants per group, for a total of 156 participants. This calculation was performed using PASS software (version 15.0).

### Statistical analysis

2.13

All analyses will adhere to the Intention-to-Treat (ITT) principle. The baseline characteristics will be summarized descriptively by group using means (standard deviations) or medians (interquartile ranges) for continuous variables and frequencies (percentages) for categorical variables to assess between-group comparability.

For the primary outcome, the cycle ovulation rate (COR) at Week 12, any missing data will be handled using multiple imputation by chained equations (MICE) with 20 imputed datasets, and results combined using Rubin’s rules (35). The COR will be compared between groups using a linear mixed-effects model with study center as a random effect. The result will be presented as the mean difference between groups with its 95% confidence interval. As a sensitivity analysis, a per-protocol (PP) analysis will be performed, including only participants who completed the 12-week intervention with adequate adherence (defined as receiving ≥80% of the scheduled acupuncture sessions) and without major protocol violations.

To assess the sustainability of the treatment effect, the COR at Week 12 and Week 24 will be analyzed together using a linear mixed-effects model for repeated measures, including group, time point (Week 12, Week 24), and group-by-time interaction as fixed effects, with study center and participant as random effects (36).

The analyses for secondary outcomes will be conducted using available data. Continuous outcomes will be analyzed using Analysis of Covariance (ANCOVA), adjusting for corresponding baseline values and study center (37). Binary outcomes will be analyzed using generalized linear mixed models, incorporating study center as a random effect (38). All statistical tests will be two-sided, and a p-value < 0.05 will be considered statistically significant. All analyses will be performed using SAS software (version 9.4, SAS Institute Inc., Cary, NC, USA).

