**Figure 1 f1:**
[figure not shown]
Flow diagram of the trial. PCOS, polycystic ovary syndrome; MA, manual acupuncture; SA, sham acupuncture; ITT, intention-to-treat; PP, per-protocol.

**Table 1 T1:** Schedule of enrollment, interventions, and assessments.

Study period	Screening	Baseline (Week 0)	Intervention (Weeks 1-12)	Post-treatment (Week 12)	Follow-up (Week 24)
Enrollment					
Eligibility Screening	X				
Informed Consent	X				
Randomization		X			
Interventions					
Manual Acupuncture			3 sessions/week		
Sham Acupuncture			3 sessions/week		
Assessments					
Cycle Ovulation Rate				X	X
Menstrual Calendar*	X	X		X	X
Reproductive Hormones (FAI, LH/FSH)		X		X	X
Metabolic Parameters		X		X	X
Anthropometrics (BMI, WC, HC, WHR)		X		X	X
Questionnaires (PCOSQ, SAS, SDS)		X		X	X
PGIC				X	X
Adverse event			Each visit	X	X
Blinding Assessment				X	
Adherence to treatment				X	X

BMI, body mass index; FAI, free androgen index; FSH, follicle-stimulating hormone; HC, hip circumference; LH, luteinizing hormone; PCOSQ, Polycystic Ovary Syndrome Quality of Life Questionnaire; PGIC, Patient Global Impression of Change; SAS, Self-Rating Anxiety Scale; SDS, Self-Rating Depression Scale; WC, waist circumference; WHR, waist-to-hip ratio.

*At Screening, participants recall their menstrual patterns over the prior 12 months to confirm eligibility (cycle length consistently between 35 and 60 days). At Baseline (Week 0), a paper calendar is provided for prospective daily recording thereafter.

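### Neither model for cycle ovulation rate uses baseline cycle length, which is already collected and likely to be prognostic: a free but modest gain in precision is left unused

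*Protocol article*

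**What the plan says.** Section 2.13 (Statistical analysis) specifies the primary comparison: "The COR will be compared between groups using a linear mixed-effects model with study center as a random effect". The result is reported as a mean difference with a 95% confidence interval. The joint Week 12/Week 24 model lists group, time point and their interaction as fixed effects, with centre and participant as random effects. Neither model names a baseline covariate. In the same section, continuous secondary outcomes are analysed by ANCOVA, "adjusting for corresponding baseline values and study center".

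COR has no baseline value of its own, since Table 1 schedules it at Weeks 12 and 24 only. A related measure does exist before randomisation. The footnote to Table 1 says that at screening "participants recall their menstrual patterns over the prior 12 months to confirm eligibility", the criterion being cycles of 35–60 days. Section 2.9.2 already uses the self-reported baseline as the comparator for mean cycle length. Randomisation (section 2.6) is stratified by centre only.

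**The concern.** Section 2.9.1 defines COR as the share of 28-day windows with confirmed ovulation, with a denominator of three for women who complete treatment. With at most one ovulation per cycle, a woman with long cycles has fewer chances to fill three windows in 84 days than a woman with short ones. Pre-trial cycle length should therefore carry information about COR in both arms. A model that ignores it leaves that variation in the residual and gives a wider interval than the collected data allow. At stake is the precision of the primary estimate, not its validity.

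**Working it through.** **1. The plan's own figure.** Inputs from section 2.12: "we anticipated a COR of 65% in the MA group and 40% in the SA group at the end of the treatment"; two-sided alpha 0.05; power 80%; chi-square test. With pooled variance and no continuity correction,

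n = [1.960 × √(2 × 0.525 × 0.475) + 0.842 × √(0.65 × 0.35 + 0.40 × 0.60)]² / 0.25² = (1.384 + 0.575)² / 0.0625 ≈ 61.4, so 62 per group.

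Then 62 / 0.80 = 77.5, so 78 per group and 156 in total. The stated figures reproduce and do not depend on covariate adjustment.

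**2. Direction of the link.** A woman with constant cycle length L has about 84/L cycles in 84 days. With at most one ovulation per cycle, her mean COR is limited to roughly (84/L)/3 = 28/L.

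| L (days) | 84/L | 28/L |
|---|---|---|
| 35 | 2.40 | 80% |
| 47.5 | 1.77 | 59% |
| 60 | 1.40 | 47% |

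Expected COR therefore falls across the eligible range, provided on-study cycles resemble pre-trial ones.

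**3. How much of COR cycle length explains.** The protocol gives no R-squared, no SD of COR and no distribution of cycle length, so these are assumptions. The simulations used 20,000 women per scenario, a within-woman SD of 5 days, ovulation 14 days before the next bleed, and a per-cycle ovulation probability either fixed at 0.75 or varying between women.

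| Assumed baseline lengths | R-squared of COR on baseline length |
|---|---|
| Uniform over 35–60 days, with or without recall error of SD 4 days | about 0.06–0.20 |
| Clustered near the short end (mean about 43 days), with or without recall error | about 0.01–0.06 |

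A second set (uniform lengths, within-woman SD 3 or 7 days, no recall error) gave 0.11–0.25 when 60–80% of cycles were ovulatory on average. Clearly higher values (0.30–0.67) appeared only when all or nearly all cycles were taken as ovulatory.

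**4. Effect on the standard error.** Adjustment multiplies it by √(1 − R²).

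- R² = 0.01: √0.99 = 0.995, a cut of 0.5%.
- R² = 0.06: √0.94 = 0.970, a cut of 3.0%.
- R² = 0.20: √0.80 = 0.894, a cut of 10.6%.

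On the 2 × 62 = 124 women expected after dropout, the equivalent gain is 124/(1 − R²) − 124: about 1, 8 and 31 women respectively.

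**5. What this means for the interval and power at 62 per group.** Take the SD of a woman's COR from three binary windows with within-woman correlation ρ: SD² = 0.23375 × (1 + 2ρ)/3, where 0.23375 is the mean of 0.65 × 0.35 and 0.40 × 0.60. The 95% half-width is 1.96 × SD × √(2/62), and power is for a 25-point difference.

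| ρ (assumed) | SD | Unadjusted half-width; power | R² = 0.05 | R² = 0.20 |
|---|---|---|---|---|
| 0.2 | 0.330 | 0.116; 0.988 | 0.113; 0.991 | 0.104; 0.997 |
| 0.6 | 0.414 | 0.146; 0.920 | 0.142; 0.932 | 0.130; 0.964 |
| 1.0 (worst case) | 0.483 | 0.170; 0.821 | 0.166; 0.840 | 0.152; 0.896 |

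Unadjusted power is above 80% in every row. Adjustment narrows the interval; it does not rescue the trial.

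**The case against.** The strongest reply is that nothing here is an error. A comparison of randomised arms with centre as a random effect is a valid primary analysis, and adding a covariate is a preference about efficiency. That stands, and it sets the weight of the point.

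Several stronger readings are tempting, and the protocol does not support them:

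- **That the estimate is biased or exposed to imbalance.** With uniform lengths and 62 per group, the 95% range of chance imbalance in mean cycle length is 1.96 × 7.22 × √(2/62) ≈ 2.5 days either way. The unadjusted confidence interval already allows for this.
- **That cycle length sets hard limits**, with at most two ovulatory windows up to about 50 days and one beyond. This holds only for perfectly constant cycles with ovulation 14 days before bleeding. With a within-woman SD of 5 days and every cycle ovulatory, roughly three in ten women at 35 days reach three windows, and roughly four in ten at 51 days reach two.
- **That cycle length is the strongest predictor of COR.** The protocol ranks no predictors.
- **That the secondary analyses contradict the primary one.** They adjust for each outcome's own baseline value, and COR has none.

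Two further objections also carry weight. Treatment is meant to change cycles: section 2.9.2 makes recovery to 21–35 days an outcome, and a COR of 65% implies cycles of about 28/0.65 ≈ 43 days or shorter in the manual acupuncture arm. If treated cycles converge, the baseline value predicts less there. Recall error and the restricted 35–60 day range also reduce the gain.

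It can also be said that covariates belong in a separate analysis plan. That would answer a complaint about missing detail. This point concerns models that the protocol already writes out.

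**Conclusion.** The point holds as a free improvement. Both stated COR models leave out a baseline variable that is already collected and has a structural reason to predict the outcome. The planned analysis remains unbiased, with its type I error intact; it gives up some precision. Under the assumed scenarios the standard error would fall by between about 0.5% (short-clustered lengths with recall error) and about 10% (uniform lengths), and by less if treatment changes cycle length. The direction is secure. The size is modest and rests on assumed R-squared values that the protocol neither gives nor allows one to derive.

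**What to change.** In section 2.13, add baseline mean cycle length (continuous, from the 12-month screening recall) as a fixed covariate in the primary COR model and in the Week 12/Week 24 COR model. Include it as a predictor in the multiple-imputation model, and report the unadjusted difference alongside. Settle this before unblinding, so that adjustment is not argued over after the baseline table is seen.

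The cost is one degree of freedom and a line of text. No new data are needed if the recalled mean is recorded as a number of days and not only as a check on eligibility. Recall error reduces the gain but does not bias the randomised comparison. The sample size stays at 156.
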